#### Sensitivity analysis for clinical outcomes

The following sensitivity analyses will be completed and reported if they change the interpretation of the findings from the main analysis described above.

• *Therapist effects:* these will be explored by adding a random effect term (to represent the treating therapist) to the main treatment models. The models with and without the therapist effect will be compared at each outcome time-point to explore the impact of the treating therapist on the effect estimates obtained.

• *Imputation of missing data:* a complete case analysis will be conducted and the results from this compared to those from imputed data.

• *Model covariates:* treatment models will be run on an unadjusted basis to investigate if the inclusion of model covariates has an impact on the main trial findings.

• *A per protocol analysis:* this will be completed on the subsample of participants receiving treatment in line with the specified treatment protocols. Criteria for determining the per protocol group assignment will be established by the Trial Management group and approved by the Trial Steering Committee before analysis begins.

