### Sample size

The sample size for the main trial will be based on the primary outcome measures: WOMAC pain and function subscales
[48] and will compare 6 months post-randomisation outcome for the usual care group with either of the two other intervention groups. We chose 6 months since our TOPIK trial
[15] showed the effects of exercise had reduced by this point with usual physiotherapy care. The BEEP trial is powered to detect an effect size of 0.35 for both WOMAC pain and function; an effect size classified as ‘small’ to ‘moderate’ using standard benchmarks by Cohen
[61]. We chose to power the trial based on a specified effect size (rather than minimum important change) as Terwee et al 2009
[62] report a lack of consensus as to minimum important change on the WOMAC. From our previous trials
[19], we estimate that the standard deviation for WOMAC pain and WOMAC function at 6 months follow-up will be 5 and 17 respectively. An effect size of 0.35 therefore equates to a 1.75 point difference on WOMAC pain and a 5.95 point difference on WOMAC function. To achieve 80% power and a 5% significance level (two tailed) we require 129 patients per treatment group, giving a total sample of 387 patients
[63]. Allowing for a 20% loss to follow-up rate (informed by our previous knee pain trials
[15,19]) we aim to randomise a total of 500 participants to the trial over a period of 18 months.

For practical reasons, the sample size will not be inflated to allow for clustering of individual patients being treated by the same physiotherapist
[64,65], but rather the trial will provide useful estimates of clustering effects and we will adjust for therapists in a sensitivity analysis. It is anticipated that a minimum of 36 physiotherapists (12 per treatment group) will be trained to deliver the trial treatments and that each physiotherapist will treat approximately 18 patients. Thus at the end of the trial, we will be able to estimate an intra-class correlation (ICC) to inform future similar trials.

A formal power calculation was not completed to determine the number of patients to wear an accelerometer. The sample size of 30 per group is based on practical considerations (restricted by the number of accelerometers available for data collection) and on having a reasonable sample size to analyse the data using parametric statistics.

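### Sensitivity analyses, including the therapist model, are reported only if they alter the reading of the main result, so a judgement of no change cannot be checked

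*Protocol article*

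**What the plan says.** In the protocol article, the section on sensitivity analysis for clinical outcomes opens with the rule "The following sensitivity analyses will be completed and reported if they change the interpretation of the findings from the main analysis described above". Four analyses follow, and the rule governs them all:

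- Therapist effects: "these will be explored by adding a random effect term (to represent the treating therapist) to the main treatment models".
- Missing data: "a complete case analysis will be conducted and the results from this compared to those from imputed data".
- Adjustment: "treatment models will be run on an unadjusted basis to investigate if the inclusion of model covariates has an impact on the main trial findings".
- Per protocol: "this will be completed on the subsample of participants receiving treatment in line with the specified treatment protocols".

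The section does not say what counts as a change of interpretation or who decides.

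The Sample size section declines, on practical grounds, to inflate the sample size for patients sharing a physiotherapist. In its place it states that "the trial will provide useful estimates of clustering effects and we will adjust for therapists in a sensitivity analysis". It adds: "Thus at the end of the trial, we will be able to estimate an intra-class correlation (ICC) to inform future similar trials".

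The sections on sources of bias and on interventions make clear that each physiotherapist delivers only one of the three treatments, so therapists are nested in arm. The primary analysis is an ANCOVA adjusted for the baseline score, age, gender, duration of the knee problem and treatment centre. Therapist is not among its terms.

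**The concern.** Whether a pre-specified analysis is reported should not depend on what it shows. Here it does, through a judgement made after the results are known and without a stated threshold. An analysis that agrees broadly but not closely with the main one, for example a similar estimate with a clearly wider interval, can be classed as no change and then disappear. Readers would know only that someone found nothing worth reporting.

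The therapist model is where this bites. It is the only planned analysis that accounts for therapists nested in arm, and the Sample size section points to it when it leaves clustering out of the calculation. Adding a therapist random effect would usually change the width of the interval more than the point estimate. Yet the protocol describes the comparison of models in terms of the effect estimates, which makes it easier to pass over a change in precision.

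The complete-case comparison also matters. The plan allows for 20% loss to follow-up, and the main analysis rests on multiple imputation.

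**Working it through.** **1. The plan's own sample size.** Inputs from the Sample size section: effect size 0.35 (1.75/5 for pain, 5.95/17 for function), 80% power, two-sided 5%.

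n per arm = 2 × (1.960 + 0.842)² / 0.35² = 2 × 7.85 / 0.1225 = 128.2, rounded up to 129. Total 3 × 129 = 387. With 20% loss, 387 / 0.8 = 484, and the plan rounds up to 500. The stated figures are reproduced, and they contain no term for clustering. The rounding leaves 500 × 0.8 = 400 analysed patients (about 133 per arm) against 387 needed, a margin of 400 / 387 = 1.034, or about 3%.

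**2. What the rule covers.** The conditional sentence stands above all four bullets, and the therapist model is the first of them. The section on data confidentiality and archiving promises publication of the trial results whatever the outcome, but does not mention sensitivity analyses. Nothing else in the article commits to reporting them unconditionally.

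**3. What the therapist model could show.** The article gives no ICC, so 0.01, 0.02 and 0.05 are assumptions. Patients per therapist (m) come from the article:

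- up to 50 therapists: 400 / 50 = 8 analysed patients each;
- at least 36 therapists: 400 / 36 = 11.1 analysed patients each;
- the stated caseload of about 18, taken at face value. This is an upper end, since 36 × 18 = 648 exceeds the 500 to be randomised.

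Because therapists are nested in arm, the variance of the treatment comparison is multiplied by about DE = 1 + (m − 1) × ICC, and the interval width by √DE.

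| m | ICC | DE | Interval width × |
|---|---|---|---|
| 8 | 0.01 | 1.07 | 1.03 |
| 8 | 0.02 | 1.14 | 1.07 |
| 8 | 0.05 | 1.35 | 1.16 |
| 11.1 | 0.01 | 1.10 | 1.05 |
| 11.1 | 0.02 | 1.20 | 1.10 |
| 11.1 | 0.05 | 1.51 | 1.23 |
| 18 | 0.01 | 1.17 | 1.08 |
| 18 | 0.02 | 1.34 | 1.16 |
| 18 | 0.05 | 1.85 | 1.36 |

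For example, with m = 11.1 and ICC 0.05: DE = 1 + 10.1 × 0.05 = 1.51, and √1.51 = 1.23. Even the smallest DE in the table (1.07) exceeds the 1.034 margin from rounding up to 500.

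These factors show the size of shift that could sit behind an unreported judgement of no change. They do not predict what the trial will find. The primary model adjusts for treatment centre, which may absorb some between-therapist variation, so the real widening could be smaller. No comparable figure can be derived from the article for the complete-case, unadjusted or per-protocol analyses.

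**The case against.** The strongest reply is that the rule works in the safe direction. It requires disclosure of any analysis that alters the interpretation and lets only agreeing results go unreported, so silence itself carries information. This stands. A reader might infer that the plan allows unfavourable results to be hidden, but the text does not say so. If the therapist model overturned a conclusion, the rule would require that to be reported. What remains is that silence cannot be checked and says nothing about how close the results were.

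A reader might also see a contradiction with the Sample size section. There is none in the strict sense. That section says therapists will be adjusted for in a sensitivity analysis, and the later section lists that analysis. The ICC is not among the four items under the condition, and the sentence about it says that it can be estimated, not that it will be reported. The two sections pull against each other in purpose: clustering estimates meant for future trials are of use only if published.

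Two further inferences go too far. One is that only the therapist model has valid standard errors. That presumes an ICC above zero, whereas the article says only that therapist effects will be explored. The other is that the primary test has a known excess error rate. At m = 11.1 the assumed ICCs of 0.01, 0.02 and 0.05 would give 2 × (1 − Φ(1.96 / √DE)) of about 6.2%, 7.4% and 11.0%. Those figures concern leaving therapist out of the primary model. They rest wholly on assumed ICCs, and reporting the sensitivity analyses would not alter them.

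There are partial safeguards. An independent statistician verifies the primary outcome analysis, the per-protocol criteria are fixed before analysis with Trial Steering Committee approval, and the data are to be archived for secondary use. None of these puts the sensitivity results in front of the reader.

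**Conclusion.** The point holds as one of transparency. The article states a reporting rule that depends on the result and has no criterion, and it applies that rule to four pre-specified analyses. This is not a detail left to a statistical analysis plan, because the rule is written down and needs replacing. It does not make the primary analysis wrong and does not conceal results that change the conclusion.

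Its weight comes from the therapist model. On assumed ICCs of 0.01 to 0.05 and about 11 analysed patients per therapist, the interval could be about 5% to 23% wider than the primary one. It could be about 36% wider at 18 per therapist and ICC 0.05, and as little as 3% wider at 8 per therapist and ICC 0.01. Adjustment for centre may reduce all of these. Widening of this order need not overturn a conclusion, which is why it could go unseen under the present rule.

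**What to change.** Replace the opening sentence of the section on sensitivity analysis for clinical outcomes with:

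*All the following sensitivity analyses will be completed and reported (estimate and 95% CI) for WOMAC pain and function at 6 months, whatever they show, together with the therapist ICC and its confidence interval.*

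This also secures the clustering estimates that the Sample size section expects the trial to provide. The ICC needs its own interval because it will rest on a modest number of therapists (at least 36, 12 per arm).

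The cost is one sentence and one supplementary table. The analyses are already planned, and the sample size, the primary model and the conduct of the trial are unchanged.

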#### Exploratory subgroup analysis

A set of exploratory analyses will investigate the factors that moderate the effects of exercise in participants with knee pain. Models will be derived using WOMAC pain and function as the dependent variables, and intervention group and other potentially important factors (demographic, knee-specific, exercise adherence, general health, attitudes and outcome expectations for exercise will be put forward as candidate independent variables). A specific subgroup analysis with strong theoretical rationale will compare the clinical outcomes of pain and function of those who report high exercise adherence across all intervention groups (versus those who report lower exercise adherence). We hypothesise that those who report higher adherence will have improved pain and function outcomes.

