[45] and therefore we will include pedometers within the suite of options for physiotherapists to give participants who wish to target increases in walking activity.

The BEEP trial protocol for Targeted Exercise Adherence will begin with a focus on the lower limb (as in the Individually Tailored Exercise group) but transitions to focus increasingly on general physical activity adherence over time. In addition to prescribing an individualised, progressed and supervised lower limb exercise programme, physiotherapists will assess patients’ current general physical activity levels, their intentions to increase their physical activity levels, their attitudes to exercise for knee pain and general health and explore their individual barriers and potential facilitators to exercise. This group will receive 4 treatments up to week 12 and a further 4 to 6 contacts from week 12 through to 6 months (a total of 8 to 10 treatment contacts). In the first 4 treatments, the aim will be for participants to initiate and progress an exercise programme with supervision that will include lower limb and general exercise, and to identify (with the support of the physiotherapist) general physical activity opportunities within the local community that are suitable for, and interest, the individual. Pro-active follow-up from the physiotherapist will take place from week 12 through to 6 months, using choices of telephone and face-to-face contact, providing an additional 4 to 5 contacts with each participant. The aim is to enhance long-term exercise adherence, promote increased general physical activity and encourage participants to develop an exercise ‘habit’, shifting the focus away from lower limb exercise in the earlier treatment sessions and towards sustainable lifestyle changes in physical activity in later treatment sessions. The follow-up sessions will ascertain and promote exercise adherence, increases in physical activity levels, support patients to integrate exercises into their activities of daily living, allow repetition and amendment of the exercise programme based on individuals’ experiences or concerns and progression at a pace suitable for the individual. The adherence enhancing ‘toolkit’ contains different educational and behavioural tools for facilitating physical activity behaviour change, selected for use based on an individualised assessment of each patient. As our Cochrane review identified that no one model of behaviour change was superior for facilitating adherence to exercise for chronic musculoskeletal pain, different theoretical models have underpinned the development of the toolkit, including self-efficacy

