#### Follow-up

Outcome measures will be collected by self-report, postal questionnaire before randomisation and at 3, 6, 9, 18 and 36 months (Figure 
1). Therefore, adherence to exercise will be measured twice throughout the early phase (0 to 6 months) and three times during the maintenance phase of the exercise interventions (9 to 36 months). Non-responders will be followed up using our standardised CTU follow-up procedures for trials. This comprises a questionnaire, a reminder postcard at two weeks and a further copy of the questionnaire at four weeks. For participants who do not respond to any of these reminders, we will aim to collect minimum outcome measure data via telephone (by research nurses who are blind to treatment allocation) and post at key outcome time-points (6 months, 18 months and 36 months) in order to try to capture primary outcome data and to minimise missing data. Quality assurance processes within the CTU will ensure training and auditing of the research nurses conducting minimum data telephone calls. In order to reduce participant burden the 3 and 9 month questionnaires will be slightly shorter than those at 6, 18 and 36 months and as direct measures of physical activity may themselves increase physical activity similar measures of physical activity will be used in each intervention group. Table 
2 includes a list of all measures and the time-points at which they will be collected.

**Table 2 T2:** Outcome measures

**Data collection**	**Measurement scale**	**Time points (months)**
*Participant characteristics*		
Age	Years	0,3,6,9,18,36
Gender	Female/Male	0,3,6,9,18,36
Weight	Stones and lbs or Kilograms	0,3,6,9,18,36
Height	Feet and inches or centimeters	0
Marital status	Married/separated/divorced/widowed/cohabiting/single	0
*Work factors*		
Current/most recent job title	Free Text	0,6,18,36
Currently in a paid Job	Yes/No	0,6,18,36
Working hours	Working full time (30 hours or more per week)/working part time (29 hours or less per week)/	6,18,36
Time off because of knee pain including time off to visit any health care professional	Yes/No (during last 6 months)	6,18,36
How many days weeks, weeks or months were you absent from work due to knee problem	Number of days/weeks/months (during last 6 months)	6,18,36
*Knee Problem*		
Knee with most discomfort	Tick boxes for left or right	0,3,6,9,18,36

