Duration of knee problem	In the last 12 months/More than 1 year but less than 5 years ago/More than 5 years but less than 10 years ago/I have had this knee problem for more than 10 years	0
Global assessment of change in knee problem	Completely recovered/much better/better/no change/worse/much worse (since first seen by the physiotherapist)	3,6,9,18,36
Knee pain^α^	0–20	0,3,6,9,18,36
Stiffness^α^	0-8	
Function^α^	0 - 68	
	(WOMAC [48])	
Illness perceptions^α^		0,3,6,
- Consequences	0-10	
- Timeline	0-10	
- Personal control	0-10	
- Treatment control	0-10	
- Identity	0-10	
- Concern	0-10	
- Understanding	0-10	
- Emotional response	0-10	
	(IPQ-brief modified for knee pain [54])	
*Physical Activity & Exercise*		
Experience of exercise	Personal experiences of exercise	0
Use of local facilities^α^	Use of local facilities for physical activity in the last 7 days	0,3,6,9,18,36
Self-efficacy for exercise^α^	0-10 (SSE scale [55])	0,3,6
Outcome expectations for exercise^α^	1-5 (OEE-2 [56])	0,3,6
Physical activity^α^	0-400+ (PASE [51])	0,3,6,9,18,36
Exercise adherence and treatment credibility	Confidence in and adherence to treatment plan	3,6,9,18,36
Accelerometry^α^	Average counts per minute	For a sub-sample of participants 0,3,6,9,18,36
	Meeting physical activity guidelines [60]	
*General health and well being*		
Depression^α^	0-24 (PHQ8 [58])	0,3,6,18,36
Anxiety^α^	0-21 (GAD7 [57])	0,3,6,18,36
Quality of life^α^	-0.59-1 (EQ-5D-3 L [59])	0,3,6,9,18,36
Body manikin (pain)	Body area shaded to represent pain last a day or longer in the last 4 weeks	0
Co-morbidity	Tick boxes for key co-morbidities	0
*Managing your knee problem*		
Current medication for knee problem	Prescribed and over the counter medications (with dosage and length of supply)	0,3
Prescribed medication for knee problem	Prescribed medications in the last 6 months/12 months/18 months (with dosage and length of supply)	6,18,36
Cost of over the counter treatments/appliances	e.g. painkillers, anti-inflammatory drugs, TENS machine, hot and cold packs, knee supports (£ in the last 6 months/12 months/18 months)	6,18,36
Costs for use of local facilities/opportunities involving physical activity	(£ in the last 6 months/12 months/18 months)	6,18,36
Healthcare Utilisation	Contact with NHS and private healthcare professionals, number of visits/inpatient stays, types of investigations/treatments in the last 6 months/12 months/18 months	6,18,36

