#### Analysis of adherence data

Descriptive statistics will be used to examine exercise adherence and will be reported as numbers and percentages, or means and standard deviations, as appropriate. Exercise adherence will be measured by reporting the number of treatment sessions attended in each treatment group, and by reporting the following measures at each follow-up time-point:

• Self-reported exercise adherence (measured by agreement with the statement ‘I have been doing my exercises as often as I was advised’)

• Frequency and duration of physiotherapy exercise completed by the participant

• Change (from baseline) in level of physical activity (measured by PASE and, in a subsample of participants, accelerometry)

• Use of local exercise and physical activity facilities

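### Exercise adherence, measured only after randomisation, is planned as a moderator and a subgroup; the comparison is a non-randomised association and cannot show moderation

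*Protocol article*

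**What the plan says.** All references are to the Protocol article.

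- **Exploratory subgroup analysis.** The aim is stated as moderation: "A set of exploratory analyses will investigate the factors that moderate the effects of exercise in participants with knee pain". The models take WOMAC pain and function as dependent variables. Intervention group and other factors are the independent variables, and among them "exercise adherence, general health, attitudes and outcome expectations for exercise will be put forward as candidate independent variables".
- The same section adds one named subgroup analysis, for which it claims a firm theoretical basis. It "will compare the clinical outcomes of pain and function of those who report high exercise adherence across all intervention groups" against those reporting less, with a directional hypothesis: "We hypothesise that those who report higher adherence will have improved pain and function outcomes".
- **Follow-up.** The text says that "adherence to exercise will be measured twice throughout the early phase (0 to 6 months") and three times afterwards. In Table 2 the row "Exercise adherence and treatment credibility" is scheduled at months 3, 6, 9, 18 and 36, with no month 0.
- **Analysis of adherence data.** Several measures are listed. One is agreement with the statement "I have been doing my exercises as often as I was advised". Others are frequency and duration of exercise, change in physical activity, and use of local facilities.
- **Secondary outcomes.** Exercise adherence is itself one of the secondary outcomes.
- **Intervention 3 (TEA).** This arm exists to raise long-term adherence. Its content changes over time, "shifting the focus away from lower limb exercise in the earlier treatment sessions and towards sustainable lifestyle changes".

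**The concern.** A moderator of a randomised effect has to be fixed before treatment can alter it. The arms can then be compared fairly at each level of the factor. Adherence does not meet that condition here: it arises after allocation and one arm is designed to change it. High and lower adherers are groups that participants sort themselves into, partly because of the arm they were given and partly because of how they are doing.

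What is at stake is interpretation. Adherence is the mechanism behind one of the two test interventions. A difference between adherers and non-adherers, reported as a pre-specified subgroup result with a hypothesis attached, would invite the reading that adherence causes better outcomes or modifies the effect of exercise. A null result would invite the opposite reading. The planned contrast supports neither.

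**Working it through.** **1. The plan's own figures.** The protocol gives no figure for the adherence comparison, so the only figures to reproduce are those of the main sample size. With effect size 0.35, 80% power and two-sided 5%: n = 2 × (1.960 + 0.842)² / 0.35² = 128.2, so 129 per arm and 387 in total. Allowing for 20% loss, 387 / 0.8 = 484, which 500 covers. These reproduce and are not in dispute. The SDs used below (5 for pain, 17 for function) come from the same section.

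**2. Can adherence define a subgroup or moderator?**

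| Requirement | What the protocol says |
|---|---|
| Measured before randomisation | First value at month 3 (Table 2) |
| Not affected by the allocated arm | Raising it is the aim of TEA |
| Not itself an outcome | Listed among the secondary outcomes |
| Unrelated to other causes of the outcome, if read causally | The Background links it to self-efficacy, motivation, age, gender and disease status |
| Not driven by the outcome, if read causally | The TEA section says patients give up lower-limb exercises when symptoms ease |

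The first three rows rule it out as a moderator or subgroup. The last two rule out an unqualified causal reading of the association.

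**3. What the contrast estimates.** Moderation by a factor X, for ITE (Individually Tailored Exercise) against usual care, is a difference of differences:

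[mean(ITE, X high) − mean(UC, X high)] − [mean(ITE, X low) − mean(UC, X low)].

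The planned comparison is mean(high adherers) − mean(lower adherers), pooled over arms. That is a main effect of X. It would not test moderation even if X were a baseline variable.

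**4. Direction of bias.** Confounding by self-efficacy or motivation could make high adherers look better. Stopping once symptoms ease would leave those still exercising with more pain, so high adherers would look worse. The protocol supports both routes and does not say which dominates, so the net sign is unknown.

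**5. Size, as an illustration only.** Assume adherence has no causal effect, that a normal latent adherence variable correlates r with the outcome, and that the split is at the median. The means above and below a normal median differ by 2 × √(2/π) = 2 × 0.798 = 1.596 SD. The spurious unadjusted gap in absolute value is 1.596 × r × SD of the outcome.

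| Assumed absolute r | Pain gap (SD 5) | Function gap (SD 17) | Share of simulated trials with p < 0.05 |
|---|---|---|---|
| 0 | 0 | 0 | 5% |
| 0.1 | 0.8 | 2.7 | 35% |
| 0.2 | 1.6 | 5.4 | 90% |
| 0.3 | 2.4 | 8.1 | 99.9% |

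The last column is from a simulation for pain with 400 participants (80% of 500). A correlation of 1.75 / (1.596 × 5) = 0.22 would match the whole 1.75-point difference the trial is powered for. The sign of r, and so of the gap, is open.

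**The case against.** The section is titled and described as exploratory, and the trial's conclusions rest on the intention-to-treat comparisons of each intervention with usual care. The hypothesis can be read as a statement of association only. Interaction terms, cut-points and the exact adherence measure are details that an article may leave to the analysis plan. All of this is fair, and it limits the weight of the point. It does not remove it: the article itself names adherence as a candidate in a search for moderators and calls the pooled contrast a subgroup analysis. Adding covariates in a later document would not turn a post-randomisation variable into a moderator.

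The calculation is also open to challenge. The correlation, the normal latent variable and the median split are assumptions. The main models adjust for baseline score, age, gender, duration and centre; if the adherence contrast carries the same adjustment, confounding through baseline severity would be smaller. That stands, and the figures are illustrative for this reason.

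Four stronger readings are tempting but not supported:

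- A reader might infer that the analysis is almost bound to confirm its hypothesis, because people in less pain exercise more. The TEA section points the other way.
- A reader might infer that nothing in the section can identify moderators. Demographic, knee-specific, general-health and outcome-expectation factors have month-0 values and remain proper candidates.
- A reader might infer that pooling necessarily mixes different quantities, because one item is relative to advice that differs by arm. That applies if that item is used; the section does not say which measure is meant, and frequency and duration of exercise are also listed.
- A reader might infer that moderation cannot be studied because every arm exercises. The effects can be read as contrasts of ITE and TEA with usual care.

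**Conclusion.** The point holds for the adherence part of the exploratory analysis. Adherence cannot serve as a moderator or as a subgroup of the randomised comparison, and the pooled contrast of high with lower adherers cannot show moderation. It is an observational association that could support or hide the stated hypothesis whatever the true effect of adherence. This rests on the measurement schedule, the outcome list and the aim of TEA, all stated in the protocol, and on no numerical assumption.

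The possible size does rest on assumptions. For correlations of 0.1 to 0.3 in absolute value, an unadjusted median split gives about 0.8 to 2.4 WOMAC pain points in either direction with no causal effect at all. The upper part of that range exceeds the trial's 1.75-point target difference. The true correlation is not known from the protocol.

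The change is worth making but not critical: the analysis is exploratory and the primary intention-to-treat result is untouched.

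**What to change.** 1. Restrict candidate moderators to baseline variables. Some candidates, such as outcome expectations, are also collected at follow-up, so state that the month-0 value is used. Test each as an arm-by-baseline interaction, for ITE versus usual care and for TEA versus usual care.
2. Remove exercise adherence from the list of candidate moderators.
3. Re-label the adherence comparison as an exploratory, non-randomised association. Estimate it within arm, or with arm adjusted for, using adherence measured before the outcome (for example month-3 adherence and month-6 WOMAC). Adjust for baseline WOMAC, baseline PASE, baseline exercise self-efficacy and the a priori covariates.
4. Use baseline rather than later values of PASE and self-efficacy: change in PASE is listed as an adherence measure, and self-efficacy is part of the proposed mechanism. Month-3 WOMAC is measured together with month-3 adherence and may be affected by it, so adjustment for it should be at most a sensitivity analysis.

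The cost is analysis wording and a few covariates that Table 2 already collects. There are three downsides. The exploratory result will be less striking. Residual confounding will remain. Month-3 adherence also does not capture TEA's follow-up phase from week 12 to 6 months, and the report should say so.
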